## Abstract

**Background:**

Schools are an ideal setting for enhancing mental health literacy, a crucial strategy for improving adolescents’ mental health knowledge and attitudes and promoting help-seeking. "*The Guide Cymru"* program is an adaptation of the mental health literacy program*" The Guide"* that was developed in Canada. The program will be culturally adapted for 13- to 15-year-old Iranian adolescent students in the first secondary schools.

**Methods:**

In this randomized controlled trial, using the stratified random sampling procedure, the whole eighth and ninth grade student body (aged 13 to 15) from Sirjan City's first secondary schools will be included in the study. Twenty first secondary schools will be randomly assigned to one of two groups: control or intervention. Finally, 562 students and 40 teachers will participate in the research. The tools of mental health literacy scale (MHLs), mental health general knowledge and attitudes related to mental disorders/illnesses are employed in this study.

**Discussion:**

This trial aims to be to explore whether "*The Guide Cymru"*, a mental health literacy program offered to students as part of the school curriculum, can decrease the stigma associated with mental health and promote help-seeking behaviors among students.

## Background

Adolescent mental health has received a great deal of attention and has been brought up as a public health concern [1]. Mental health issues are estimated to affect 10 to 20 percent of adolescents and children [2]. Adolescents' performance, development, and wellbeing alike can all be influenced by poor mental health [3]. if neglected, it may progress into adulthood and cause physical and mental issues [4]. Despite the high prevalence of mental health problems among adolescents, proper help-seeking for such concerns is uncommon [3]. In fact, there is a need to enhance help-seeking in order to reduce the rising prevalence of mental health problems among adolescents as well as to promote mental health literacy as a key strategy for help-seeking promotion among adolescents [5, 6]. Mental health literacy is an evolving concept that has been conceptualized in various ways from the time Jorm Jorm, Korten [7] coined the term in 1997 [8, 9]. In past years, mental health literacy has shifted from focusing on mental illness and risk factors to becoming an asset for health [10]. A more recent definition of MHL includes four components: [1] understanding how to obtain and maintain good mental health; [2] understanding mental disorders and their treatments; [3] decreasing the stigma associated with mental disorders; and [4] enhancing help-seeking efficacy (i.e., knowing when and where to obtain evidence-based mental health care and possessing the competencies to enhance self-care) [11].

Adolescence is a time when significant increases in the diagnosis of mental disorders are observed. In the survey of psychiatric disorders among children and adolescents in Iran (2016), the general rate of occurrence of psychiatric disorders was reported to be 10.55% [12]. In 2019 national survey of children and adolescents, which looked at the prevalence of mental diseases; 22.31% of Iranian children and adolescents had at least one psychiatric disorder [13]. Therefore, an increasing trend was observed in the prevalence of mental disorders among Iranian children and adolescents. Psychiatric disorders grouped in the category of anxiety disorders with a prevalence of 14.13% were the most frequent mental disorders among all children and adolescents; this category included the separation anxiety (5.34%), special phobia (4.84%), obsessive compulsive disorder (3.48%), agoraphobia (2.86%), general anxiety (2.57%), social phobia (1.8%), posttraumatic stress disorder (0.5%), and panic disorder (0.2%) [13].

Really, the high prevalence of mental disorders justifies the special attention of health systems to the mental health status of children and adolescents. Therefore, providing the adolescents with skills to manage their mental health as well as assisting to others, including peers is critical [14]. Inasmuch as adolescents frequently prefer to seek assistance from their peers for mental health issues, mental health education should be an ongoing component of the school curriculum [2]. Considering the vital role of education in mental health literacy, schools will provide an appropriate setting for educating vulnerable people about their mental health literacy. The reason is that adolescents spend the majority of their time in school, and education is inextricably associated with health [15]. Furthermore, a teacher with a strong and persuasive personality can play an important role in fostering students' mental health literacy by helping them to have the courage and confidence to discuss their mental health with a trusted one [3]. Evidences indicate that schools are ideal venues to address and enhance various aspects of mental health literacy in both students and teachers [16]. The results of studies in Canada [14], Cambodia and Vietnam [17], Wales [3] and Nicaragua [18] regarding the effectiveness of *The Guide* program in improving mental health literacy in high school students showed that the mental health literacy and the knowledge and attitude of students were increased after the implementation of the program in the classroom. In addition, the knowledge and attitude of mental health literacy among teachers increased significantly [18].

Nonetheless, health professionals and policymakers have recognized the significant role of schools in addressing the mental health requirements of adolescents [19]. Therefore, a mental health literacy program provided as part of the school curriculum to students can reduce the stigma associated with mental health and increase help-seeking behaviors for mental health concerns [20].

### The Guide Cymru

The school-based mental health literacy program, adapted and modified from the original Canadian handbook [21], was designed to improve the knowledge and attitudes of 13–15-years-old high school students about mental health. *The Mental Health and High School Curriculum Guide (The Guide)* is a school-based mental health literacy resource developed by mental health experts, educators and the Psychiatric Unit of Health Canada [22].

The school-based mental health literacy program guide is the only scientific mental health curriculum resource demonstrating that students' mental health literacy can be enhanced through teacher training programs as well as their applications in various programs. It is noteworthy that this edition of *The Guide* has supplanted all previous editions and has been rewritten with new contents [6]. *The Guide* has been settled to help students enhance their knowledge of mental health and is used in the first year of secondary school (aged 13 to 15). Usually, mental disorders onset during adolescence; so it is crucial that adolescents have the required knowledge, attitude, and skills to assist themselves and others when necessary.

Mental health literacy includes four components of 1) understanding how to obtain and maintain good mental health; [2] learning about mental disorders and their treatments; [3] decreasing the stigma associated with mental disorders; and [4] enhancing help-seeking efficacy (i.e., knowing when and where to obtain evidence-based mental health care and possessing the competencies to enhance self-care).*The Guide* assists students in achieving success in each of these areas. It should be noted that *The Guide* as mental health literacy resource is taught in 8 to 12 class hours using a combination of instructional methods, group discussion, group activities, self-directed learning, and videos.

The *Guide Cymru* covers six areas including: 1) Understanding mental health and mental illness, 2) Stigma of mental illness, 3) Information about specific mental illnesses, 4) experiences of mental illness, 5) seeking and receiving support, and 6) the importance of positive mental health [13]. Furthermore, *The Guide* includes material for teacher self-study, which provides them with an in-depth comprehension of the subject matter they teach. The important point is that teachers who utilize *The Guide* in their classes go through a training session to get acquainted with the material.

## Objectives

### Primary objective

The primary purpose of this study is translation and cultural adaptation of the school-based mental health literacy program guide as well as validation of the *Guide Cymru* program in Iranian adolescent students aged 13–15. Also, the study deals with with the implementation and evaluation of program.

### Practical objective

Following the translation and validation, *The Guide* will be utilized as a national protocol for the mental health curriculum in the first secondary level. Additionally, *The Guide* will be utilized by teachers who have been educated in its usage to raise the mental health literacy of first secondary students aged 13–15.

## Methods/design

### Design of the study

The present study is a randomized controlled trial with the aim of validating and evaluating the *Guide Cymru* school-based mental health literacy training program in Iranian adolescent students aged 13–15 in 2023.

### Population and sampling

The study population includes all adolescents in grade 8th and 9th year of secondary schools (13 to 15 years old) using stratified random sampling from Sirjan city; a city in Kerman province in the southeast of Iran. Using the effect size and primary data of Nguyen, Dang [17] study and considering the first type error at the level of 0.05 and the power of 0.80, the sample size was calculated to be 281 students in each of the intervention and control groups. Finally, 562 students of the first secondary schools of Sirjan city will be included in the study.$${n}_{1}={n}_{2}=\frac{\left({S}_{1}^{2}+{S}_{2}^{2}\right){\left({Z}_{1-\frac{a}{2}}+{Z}_{1-\beta }\right)}^{2}}{{\left(\overline{{X }_{1}-\overline{{X }_{2}}}\right)}^{2}}$$

After receiving the list of first secondary schools from the Department of Education, in order to prevent the effect of the intervention and based on the three geographic regions of Sirjan, a total of 20 first secondary schools will be randomly divided into two groups of control and intervention. This number of schools was determined based on the assumption that each school has a minimum of 28 students to be included in the study. According to the procedure for implementing the intervention, two teachers (a health coach and an educational coach) will be chosen from each school. Twenty teachers from each of the two groups (intervention and control) will take part in the study, for a total of 40 teachers. If a teacher expresses unwillingness, will be replaced by another teacher.

## Recruitment and selection

### Inclusion and exclusion criteria

#### Eligible schools

The public schools of Sirjan city, wishing to implement the educational intervention of the mental health literacy program for the grades of 8th and 9th, and introduce two teachers to the two-day educational program as well as provide the essential conditions for their involvement will be included. Eligible students are also students in the age group of 13 to 15 years, studying in the 8th and 9th grades in a public school in Sirjan.

#### Exclusion criteria for schools

Exceptional schools with students of learning disabilities or behavioral problems as well as non-profit schools.

After receiving the code of ethics, permission and letter of introduction from the Research Vice-Chancellor of Shahid Sadougi University of Medical Sciences, Yazd, the necessary coordination was done with the education department of Sirjan city. In the following, the names of the instructors engaging in the study were determined and after describing the objectives of the study and expressing willingness, they were invited to collaborate as facilitators in this study. The research team then invited all included teachers to attend a two-day training course for the mental health literacy program. The training course was held with the presence and supervision of a psychiatric specialist to ensure the quality of the course and the specialization of mental health issues.

#### Design of the study

In this study, the validation and evaluation of school based mental health literacy educational program, the Guide Cymru will be conducted on adolescent students aged 13 to 15 according to Fig. 1. Shows the procedure to be followed.

**Fig. 1 Fig1:**
[figure not shown]
Procedure of school-based mental health literacy program *The Guide Cymru*

#### Study phases

Followings are the procedures for conducting the study in two phases:

Phase 1: Translation and cultural adaptation of the mental health literacy program* "The Guide Cymru".*A) Translation and cultural adaptation of *"The Guide Cymru".*b) Accreditation of the school-based mental health literacy training program "The Guide Cymru".c) Suitability and readability assessment of materials (SAM & RAM).d) Validity and reliability of general mental health knowledge and attitudes related to mental disorders/illnesses.Phase 2: Implementation of the educational program and evaluation of the school-based mental health literacy program *"The Guide Cymru".*Step 1) Pre-test.Phase 2) Empowering teachers in mental health literacy based on school-based mental health literacy program *"The Guide Cymru".*Step 3) Implementation of an educational program for students based on school-based mental health literacy program *"The Guide Cymru".*step 4) Evaluation of the impact of school-based mental health literacy program *"The Guide Cymru".*

## Implementation of phase 1

### Translation and cultural adaptation of Mental Health Literacy Guide *"The Guide Cymru"*

Prior to start the study, we will communicate with *"The Guide Cymru"* developers to get their permission to translate it into Persian. Then, in the first step, the mental health literacy guide will be translated into Persian as well as culturally adapted according to the guide of Beaton, Bombardier [23] guide. In the next step, the form and content Validity and reliability of general mental health knowledge and attitudes related to mental disorders/illnesses which are available in *The Guide* are tested.

### A) Translation and cultural adaptation of *"The Guide Cymru"*

After receiving written permission from the guide's primary developers via email, the translation process will commence. The translation approach used in this study is based on the IQOLA standard procedure, which comprises translation phases, translation quality evaluation, reverse translation, and a comparison of the English and Persian versions by the guide's primary developers [24]. The first step is to translate the guide. Initially, two Persian native speakers who are both fluent in English will translate the guide into Persian without knowing one another. Then, both translations will be combined and the finest terms will be selected to create a single version. The second phase is the reverse translation, in which the Persian translation will be converted into English by two native speakers of the original language (English) who are unaware of each other as well as unaware of the original version of the scale. Then, the two versions are combined, compared, and the finest terms are chosen to form a single version. The third step is the collective review, which examines and revises the final translation in a concentrated group-discussion session with the consultation of subject-matter experts(People who have sufficient expertise in the field of tool making and its localization, as well as familiarity with the category of mental health, including clinical psychology, psychiatry, educational sciences, and health education and health promotion) for improved comprehension and in accordance with the original guide.

Finally, the final English version will be emailed to the principal developer for final approval. Regarding the conformity of the translated version with the original version, their opinions were sought and the conceptual consistency and conformity between the original version and the Persian-to -English translated version were confirmed.

### B) Validity of the school-based mental health literacy program *"The Guide Cymru"*

Educational tools must be highly applicable in real-world applications. Van Der Vleuten [25] developed five characteristics of measurement tools, namely validity, reliability, feasibility, acceptability, and educational impact. Each of these features is important to users. Tools must be valid and reliable. An unreliable instrument will not be able to track the success of training over time in a consistent and error-free manner. Acceptability considers the tool's suitability from the users' point of view. This feature not only entails measuring construct validity but also results in the feasibility of instruments and educational impact [26]. Users (students, instructors) need to know that the training program has a sufficient amount of content and that internal consistency (reliability) increases as the number of training items increases [27]. Van Der Vleuten [25]underlines the necessity of assessing all of these factors when selecting the proper instrument for the proper purpose. For example, if the outcomes of the curriculum guide are to be utilized at higher levels, it must have high reliability, educational effect, and acceptability in order to increase students' mental health literacy. The school-based mental health literacy training program validity will be determined using face validity, content validity, feasibility, acceptability, and educational impact.

### Feasibility, Acceptability, and Educational Impact

Feasibility, acceptability and educational impact of *The Guide Cymru* will be examined through a checklist of four questions with a bipolar range of excellent/completely applicable to very weak/not applicable at all, including (overall evaluation of the program, improvement of teachers' mental health literacy, improvement of students' mental health literacy, usability of educational program) in the presence of twelve mental health experts.

### Face validity

In face validity, the appearance of the tool is examined by the target group. If a tool has face validity, more motivation will be created in the target group to complete it. To assess the qualitative face validity, face-to-face interviews will be performed with ten people from the target group (five teachers and five students). The main researcher, who has complete control over the educational program, will conduct this interview. People are asked to read the educational program's guide and express their understanding of the program's educational content to the researcher. They will also be asked about the level of difficulty, i.e. difficulty in comprehending phrases and words, the degree of relevancy, i.e. the potential incompatibility of the educational program's contents from the respondents' perspective, The degree of ambiguity, i.e. the likelihood of phrase misinterpretation or semantic failure. Also, this group's recommendations will be followed, and this process will continue until people's understanding of the Training program guide is simplified and no new adjustments are requested [28].

### Assessing Content Validity Using A Qualitative Approach

In order to qualitatively assess the content validity in this study, twelve professionals with experience and education in mental health, health education, health promotion, and educational sciences will be requested to assess the guide for grammar, suitable terminology, and module content layout.

### Content Validity Ratio (CVR)

The content validity ratio is determined by gathering ratings from a group of experts, including a psychology expert, a health education and promotion expert, and an educational science expert. They are asked to assess the necessity of each item on a three-part Likert scale (necessary, beneficial but not necessary, unnecessary). In accordance with the Lawshe method and the formula below, every model demonstrates a satisfactory CVR. CVR = (Ne-N/2)/ (n/2).

### Content Validity Index (CVI)

The content validity index (CVI) will be checked using the Waltz and Basel methods. Experts will use a 4-part Likert scale to judge the "relevance" and "clarity" of each question. Then, the value of CVI will be determined by dividing by dividing the number of experts who agree with the question (on a Likert scale, scores of 3 and 4 are regarded agreeable) by the total number of experts [29]. Afterwards, the average CVI score of relevance and clarity associated with each question will be calculated and then reported. Based on the CVI score, Hyrkas et al. proposed a score of 0.79 or higher to approve each question [30].

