### Content Validity

The content validity will be determined using two qualitative and quantitative methodologies. As part of the qualitative review of the content, the final translated version of the questionnaire will be presented to ten psychometric experts to provide the required feedback after a qualitative examination of the tool based on grammar, usage of relevant words, placement of phrases in the proper location, and appropriate scoring. Also, the Content Validity Ratio (CVR) and the Content Validity Index (CVI) will be used to assess the content validity quantitatively.

With CVR, the necessity of an item is assessed by professionals so that only the most significant and correct items are chosen and CVI evaluates the clarity, adequacy, or relevance of the items with respect to the researcher's objective are evaluated from the perspective of experts, which aids in designing the items in the most effective manner to measure the content. In order to determine the CVR, the group of experts is requested to assess as well as score each item's necessity based on the three-part Likert spectrum (necessary, useful but not necessary, and not necessary). It is therefore possible to ensure the selection of the most crucial and accurate content based on the scores obtained for each item.

In addition, to check the CVI, following distribution of the tool to ten psychometrics specialists, the score obtained from their opinions on the relevance, clarity and simplicity of each item will be calculated based on a four-part Likert scale. Therefore, it is possible to ensure the selection of the most relevant, simple and clear items. The minimum acceptable value for the CVI index is 0.79, and any item with a CVI index less than 0.79 should be eliminated [30].

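### Item approval on an average of relevance and clarity lets clear wording make up for weak relevance: 7 of 12 experts can suffice where 0.79 on relevance alone would need 10 of 12

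*Protocol article*

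**What the plan says.** Two sections of the protocol article set CVI rules.

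- **Guide** (section Content Validity Index (CVI)). Experts rate each question for relevance and clarity on a four-point scale, where "on a Likert scale, scores of 3 and 4 are regarded agreeable". The CVI is the number of agreeing experts divided by all experts. Then "the average CVI score of relevance and clarity associated with each question will be calculated and then reported". The next sentence gives the approval rule by citing a source that "proposed a score of 0.79 or higher to approve each question". This section gives no panel size. The preceding section on qualitative content validity uses "twelve professionals with experience and education in mental health, health education, health promotion, and educational sciences".
- **Knowledge and attitude questionnaires** (section Content Validity). Ten psychometrics specialists take part, and "the score obtained from their opinions on the relevance, clarity and simplicity of each item will be calculated based on a four-part Likert scale". The rule is that "any item with a CVI index less than 0.79 should be eliminated". The index is in the singular, and no rule for combining the three ratings is given.

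Other screens sit alongside these. A content validity ratio (CVR) for necessity is planned for both the Guide and the questionnaires, without a numerical cut-off. The questionnaires also have an item impact score with a cut-off of 1.5 (section Determining face validity).

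**The concern.** Relevance is the content-validity question: does the item belong to what is being taught or measured? Clarity and simplicity concern wording, and an item can score full marks on both without belonging. Averaging treats the dimensions as interchangeable, so a surplus on wording pays for a deficit on relevance, and a cut-off of 0.79 no longer means that 79% of experts found the item relevant.

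The rule matters because validation of the program in Iranian students is part of the primary objective, and content validity is one of the components by which the article says it will be judged. The questionnaire rule also helps fix the Persian knowledge and attitude instruments, which are trial outcomes. The attitude scale has only 8 items, so one weak item is one-eighth of it.

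**Working it through.** **Inputs**

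- Cut-off T = 0.79 (both CVI sections).
- Guide: 2 dimensions, averaged (stated). Panel of 12: an assumption, taken from the qualitative content review. Panels of 3 to 20 were also checked.
- Questionnaires: 3 dimensions, 10 experts (stated). Averaging: an assumption, carried over from the Guide section.

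The 0.79 is a chosen cut-off with a cited source, so there is no figure of the plan's own to reproduce.

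**Formula.** If d dimensions are averaged and all but relevance stand at 1.00, the item passes when (r + d − 1)/d ≥ T, that is, r ≥ d·T − (d − 1).

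**Guide, d = 2**

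- r ≥ 2 × 0.79 − 1 = 0.58.
- 7 of 12: (0.583 + 1)/2 = 0.792, approved. 6 of 12: (0.500 + 1)/2 = 0.750, not approved.
- Relevance alone: 9/12 = 0.750 fails and 10/12 = 0.833 passes, so 10 are needed.
- Perfect clarity is not required for the offset. The average needs 0.79 × 24 = 18.96, so 19 of the 24 ratings must agree. Relevance and clarity counts of 7 + 12, 8 + 11 and 9 + 10 all pass with relevance below 0.79.
- Other panel sizes: with 10 experts, 6 suffice under averaging, against 8 on relevance alone. With 3 experts, 2 suffice, against 3.
- At any panel size, no more than 1 − 0.58 = 42% of the experts can withhold relevance agreement from an approved item.

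**Chance of approval, 12 experts, unanimous clarity.** The relevance probabilities are illustrative, not taken from the documents; experts are taken as independent.

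| Probability that an expert calls the item relevant | Average rule, P(X ≥ 7) | Relevance alone, P(X ≥ 10) |
|---|---|---|
| 0.5 | 1586/4096 = 0.387 | 79/4096 = 0.019 |
| 0.6 | 0.665 | 0.083 |

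**Questionnaires, d = 3, only if averaged**

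- r ≥ 3 × 0.79 − 2 = 0.37.
- 4 of 10: (0.4 + 1 + 1)/3 = 0.80, kept. 3 of 10: (0.3 + 1 + 1)/3 = 0.767, eliminated.
- Relevance alone: 7/10 = 0.70 fails and 8/10 = 0.80 passes, so 8 are needed.

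**Would the impact score catch that 4-of-10 item?** The impact score is the share of experts scoring 4 or 5, times mean importance. Suppose importance follows relevance, so that 4 of 10 score 4 or 5. The highest possible mean is (4 × 5 + 6 × 3)/10 = 3.8, giving 0.4 × 3.8 = 1.52, just above 1.5. One point less anywhere gives 0.4 × 3.7 = 1.48, which fails.

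**The case against.** The case on the other side has four parts.

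1. **A reader might infer that an item most experts call irrelevant can be approved.** The Guide section does not support this. Its two-way average forces at least 58% relevance agreement; with 5 of 12, the best possible average is (0.417 + 1)/2 = 0.708. The inference needs a three-way average, and the questionnaire section never states one. Applying 0.79 to each of the three ratings fits that text equally well. This objection stands, and it limits the point to what is written above.

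2. **The Guide section does not expressly tie 0.79 to the average.** It says that the average is reported and then attaches the cut-off to the CVI score. This is correct. But the average is the last per-question score defined before the cut-off, so it is the natural reading. On the other reading, the text still leaves open which CVI decides.

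3. **CVI is not the only filter.** For the questionnaires this carries weight: if importance tracks relevance, the impact score would nearly always remove the 4-of-10 item. A claim that irrelevant items will remain in the outcome scores is therefore unsupported. The CVR is less reassuring. It rates necessity, but no cut-off is printed for the Guide or the questionnaires, so whether it would remove a given item cannot be told.

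4. **The chances of approval rest on invented agreement rates.** This is so, and they serve only as illustration. The knowledge and attitude items also come from a previously evaluated instrument, so many very weak items need not be expected. The minimum counts (7 against 10 of 12) use no agreement rate; they depend only on the cut-off, the panel size and full clarity.

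**Conclusion.** The concern holds in a limited form. For the Guide, on the natural reading, averaging lowers the effective relevance requirement from 0.79 to as little as 0.58. This rests on that reading and, for the counts, on a panel of 12. For the questionnaires the finding is narrower: three ratings enter one elimination index and the text does not say how. The lower floor of 0.37 is conditional on averaging and applies to the CVI step only.

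The consequence is for the content validity of the Guide and of the knowledge and attitude questionnaires. The Mental Health Literacy Scale, already modified and confirmed in a separate evaluation, is not covered by these rules. The trial's sample size and error rates are not affected. The change is worth making because validation belongs to the primary objective and the remedy needs no new data.

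**What to change.** In both CVI sections, state that the CVI is computed separately for each dimension and that 0.79 applies to each. Keep an item only if its relevance CVI is at least 0.79 (8 of 10 experts, or 10 of 12). Reword, rather than drop, items that fail only on clarity or simplicity. Report the average across dimensions as description only. State the size of the panel that rates the Guide's CVI.

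The cost is a sentence or two in each section, using ratings already planned. The downside is that a few more items may be reworded or dropped.
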